### Primary outcomes

2.4

*Selective Mutism symptoms:* to obtain parent reports of selective mutism symptoms in their child, a) The Dutch translation of the Selective Mutism Questionnaire (SMQ) [18] and b) the selective mutism section of the Anxiety Disorders Interview Schedule [19] will be used.

For the purpose of this study, the Dutch SMQ will be validated. The SMQ consists of two scales, the symptom scale (17 items, response categories: “always”, “often”, “sometimes” and “never”), and the impediment scale (6 items, response categories: “no”, “moderate”, “fairly” and “a lot”). Within the symptom cluster, subscales for school, home and social environments are distinguished [18,20]. A higher score in the SMQ indicates more problems with speaking.

Validation of the SMQ will be based on the baseline scores (T1) of all children referred to our center for diagnosis and treatment of selective mutism.

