### Patient recruitment and procedure

2.1

Parents of eligible patients will be personally informed about the research project by the psychologist-researcher and will receive written information about the research project. Written informed consent will be obtained from parents/guardians for patients under the age of 12. From the age of 12 written consent will also be obtained from them. Only patients (≥12 years), who have given informed consent, or whose parents have signed informed consent will participate in this study.

After informed consent is provided, children are randomly assigned to treatment for selective mutism (N = 38) or the waiting list control group (WCG: N = 38).

Randomization will be stratified for gender, age (children aged until 7 years old are stratified into the “young” group, and children ages 8 and up are in the “old” group) and bilingualism (speaking one language, i.e. Dutch, versus speaking multiple languages). Randomization will be performed by an independent researcher, who will inform the therapists regarding the randomization outcome.

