*Sample size calculation*

A preliminary randomized clinical trial into behavioral treatment of selective mutism showed an effect size of Cohen's d = 0.58 on speaking in social situations [15]. To determine effects on our primary outcome (i.e. the pre versus post treatment change (T1-T3) on selective mutism symptoms), based on an effect size of d = 0.58 (medium effect size), an alpha of 0.05 (two-tailed) and a power of 0.8, a sample size of 76 (38 per group) is needed [30].

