### Intention to treat

3.2

The statistical analyses will be based on the intention-to-treat principle. If appropriate, secondary analyses will be conducted using a per-protocol basis.

Primary and secondary outcomes: Pre-post changes (pretreatment and post treatment assessment of the treatment versus WCG group) on the primary outcome (symptoms of selective mutism) will be tested with repeated measures analyses (factorial repeated measures ANOVA). To determine pre-post change in treatment outcome (responders vs. non-responders) paired sample t-tests will be executed. The effectiveness on secondary outcome measures: symptoms of anxiety/depression, self-image, quality of life and care consumption, will be tested with the same analyses. With linear and logistic regression predictors (e.g., gender, age, socio-economic status, bilingualism, parental psychopathology and parenting styles) for treatment outcome can be determined (p < .05). In the analyses, the number of treatment sessions will be included as a covariate.

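### Two instruments are named as primary but the sample size and analysis treat them as one outcome, with no rule for success, so the 5% level is not secured

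*Protocol article*

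**What the plan says.** Section 2.4 of the protocol article lists the parent-reported measures of selective mutism symptoms as "a) The Dutch translation of the Selective Mutism Questionnaire (SMQ) [18] and b) the selective mutism section of the Anxiety Disorders Interview Schedule". Table 1 has the same two rows under its primary-outcome heading, both completed by parents at T1, T2 and T3. Neither place ranks them or combines them into one score.

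The SMQ itself yields several scores. Section 2.4 states "The SMQ consists of two scales, the symptom scale" (17 items), adds an impediment scale of 6 items, and distinguishes school, home and social subscales within the symptom scale. It does not say which score is the primary one.

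Elsewhere the primary outcome is singular. The sample size calculation (at the end of section 2.5) defines it as the T1 to T3 change in selective mutism symptoms, "based on an effect size of d = 0.58 (medium effect size"), "an alpha of 0.05 (two-tailed) and a power of 0.8", giving 38 per group. Section 3.2 plans a factorial repeated measures ANOVA of pre-post change "on the primary outcome (symptoms of selective mutism"). Neither passage names an instrument or score, and neither says what pattern of results would count as success.

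**The concern.** A questionnaire score and an interview section cannot enter one repeated measures ANOVA as a single dependent variable unless a composite is defined, and none is. At least two primary analyses therefore follow, while the alpha and the power were set for one.

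Two things are at stake. The alpha of 0.05 may not be the error rate of the trial's main claim, because the team could report whichever instrument turned out favourable. Alternatively, if both instruments must show an effect, the power is lower than for a single comparison. The sample size paragraph matches the trial only if there is one named primary outcome, and the article does not name it.

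**Working it through.** **Inputs from the article.** d = 0.58, two-sided alpha 0.05, power 0.80 and 38 per group (sample size calculation); two primary instruments (Table 1, section 2.4). **Assumptions.** The correlation ρ between the two test statistics is not given, so it is varied from 0 to 0.9. The effect is taken as d = 0.58 on both instruments.

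**1. The article's own figure.** For one two-sided comparison of means, n per group = 2(z₀.₉₇₅ + z₀.₈₀)²/d² = 2(1.960 + 0.842)²/0.58² = 46.7, so 47 per group (94 in total); the exact t-test gives 48 (96). The stated 76 is not reproduced. A one-sided 0.05 t-test gives 38 per group (76). With 38 per group, the noncentrality is 0.58 × √(38/2) = 2.53, and the two-sided power is Φ(2.53 − 1.96) ≈ 0.715 (normal) or 0.704 (t). This discrepancy is a separate point, but 0.715 is the starting value for step 3.

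**2. If either instrument suffices.** With no true effect and independent tests, P(at least one p < 0.05) = 1 − 0.95² = 0.0975. For correlated statistics, from simulation (2 million draws):

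| ρ | P(at least one p < 0.05) |
|---|---|
| 0 | 9.75% |
| 0.3 | 9.5% |
| 0.5 | 9.1% |
| 0.7 | 8.3% |
| 0.9 | 7.0% |

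Splitting alpha (0.025 each) would restore 5%. Each test would then need 57 (normal) or 58 (t) per group for 80% power; with 38 per group, each has about 60%.

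**3. If both are required.** The error rate is at most 5%, because a false claim needs a false positive on an instrument with no effect, and that test alone is held at 5%. Power at ρ = 0 is 0.715² = 0.511. From the bivariate normal distribution:

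| ρ | Power, both significant, 38 per group |
|---|---|
| 0 | 51% |
| 0.3 | 55% |
| 0.5 | 58% |
| 0.7 | 61% |
| 0.9 | 65% |

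The shortfall does not depend only on the discrepancy in step 1. If 38 per group truly gave 80% power for each instrument, the power for both at ρ = 0 would be 0.80² = 0.64, and it would stay below 80% unless the two tests always agreed.

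**4. If one is named primary.** One test at two-sided 0.05 has a 5% error rate. Testing the second instrument only after the first is significant keeps the rate for the pair at 5%. Only this arrangement fits a single-outcome sample size calculation.

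**The case against.** The strongest reply is that this is a condensed article, and that scoring, test hierarchy and alpha allocation usually sit in the full protocol or the SAP. That is fair for the multiplicity method. It does not cover the identity of the primary outcome, which the article does address, and on which it disagrees with itself: two outcomes in Table 1 and section 2.4, one in the sample size calculation and section 3.2.

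It can also be said that both measures are parent reports of the same construct, so their results should be strongly correlated. That makes the lower part of the 7% to 10% range more plausible than the upper part, but does not bring it to 5%.

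A third reply is that section 3.1 aims to include 100 children. With 50 per group and no drop-out, a single two-sided test has about 82% power. Requiring both gives 0.82² ≈ 0.67 if independent, and at most 82%. Split alpha gives about 73% per test. The larger target helps but does not say what success means.

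Several stronger readings are tempting, and the article does not support them:

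- A reader might infer that each instrument is tested at 0.05. The article gives 0.05 for the one sample size comparison, and the only threshold in section 3.2 belongs to the predictor regressions.
- A reader might count the SMQ impediment scale and subscales as further primary tests, which would give much higher error rates. Section 2.4 describes these scales without declaring them endpoints. Section 2.5 announces subscale analyses for the CBCL, YSR and TRF but not for the SMQ.
- A reader might think the assumed effect, which is "on speaking in social situations", belongs to the SMQ social subscale and so misses the school setting. The abstract counts school among the social situations in which the child does not speak, and the cited trial is not available to settle it.

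**Conclusion.** The point holds as an unresolved contradiction about what the primary outcome is. The single-outcome alpha and power in the sample size calculation are not secured by the outcomes listed in section 2.4. An either-one rule would give a false-positive rate of about 7% to 10% (ρ from 0.9 to 0). A both-required rule would keep it at or below 5%, with power of about 51% to 65% at 38 per group (ρ from 0 to 0.9, d = 0.58 on both, normal approximation).

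It would go too far to say that the error rate exceeds 5%. That is true only under the either-one rule, which the article neither states nor excludes. All the correlations are assumed. Whether the primary comparison belongs at T2 or T3 is a separate matter and does not affect this conclusion.

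**What to change.** Before any between-group comparison, state in section 2.4, and repeat in the sample size calculation and section 3.2, one instrument and one score as the single primary outcome at two-sided 0.05. The SMQ 17-item symptom total is one example. The ADIS-C section would control the error equally well, and since the Dutch SMQ is still to be validated in this study, the choice should be justified. Test the other instrument next in fixed sequence, only if the first is significant. Make the SMQ impediment scale and the school, home and social subscales secondary. If the SMQ is chosen, its scoring can be fixed in time, because section 2.4 bases the validation on baseline scores.

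This costs wording only. The downside is that the second instrument can no longer carry the primary claim alone. If the team prefers an either-one rule with split alpha, or a both-required rule, it should say so and recompute the sample size. For split alpha at d = 0.58 and 80% power per test, that is 57 to 58 per group (114 to 116 in total).

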### Secondary outcomes

2.5

*Anxiety/mood symptoms*

Interview: The Anxiety Disorders Interview Schedule (ADIS-C) clinical interview is used to obtain information from parents about possible comorbid problems.

Questionnaires: Emotional and behavioral problems will be assessed by the following questionnaires, which have parallel items.

The Child Behavior Checklist (CBCL) [21,22] will be used to obtain standardized parent reports of emotional and behavioral problems in their child. The Youth Self Report (YSR) [21] is the parallel version of the CBCL, but items are formulated in the child form. Children of 11 years and older will complete the YSR.

The Dutch version of the Teacher's Report Form (TRF) [21,22] will be completed by the teacher of the child. The TRF assesses problem behavior (at school). In the CBCL, YSR and TRF questionnaires, a higher score indicates more emotional and/or behavioral problems. In these questionnaires, we are examining the internalizing and externalizing total scales as well as the subscales. The items related to (social) communication will also be examined individually.

*Self-worth image:* The Dutch version of the Self Perception Profile Child/Adolescent [23,24] is completed by children of 8 years and older.

*Quality of life:* The Dutch version of the Child Health Questionnaire (CHQ) [25,26] is used to assess quality of life of the child.

*Predictors*

*Parental psychopathology:* The Adult Self Report (ASR) [27] will be used to screen for parental emotional and behavioral problems.

*Parental parenting styles:* The Egna Minnen Beträffande Uppfostran – Parent version questionnaire (EMBU-P) [28] will be used to assess the parenting style parents use for the child.

*Demographic variables:* Demographic variables such as age, gender, socio-economic status and bilingualism will be assessed during intake, using a semi-structured interview used in care as usual.

*Health care consumption:* Previous physical and mental health consumption will be assessed during intake, using a standardized questionnaire [29].

*Treatment integrity*

To check treatment integrity, all treatment sessions will be audio/video-recorded (if consent of parents and child). Recordings will be saved safely and coded. A random 20% of all sessions will be rated by two independent raters. To avoid protocol drifting, monthly supervision will be given by a certified psychologist. The psychologists providing treatment are trained in the protocol.

*Sample size calculation*

A preliminary randomized clinical trial into behavioral treatment of selective mutism showed an effect size of Cohen's d = 0.58 on speaking in social situations [15]. To determine effects on our primary outcome (i.e. the pre versus post treatment change (T1-T3) on selective mutism symptoms), based on an effect size of d = 0.58 (medium effect size), an alpha of 0.05 (two-tailed) and a power of 0.8, a sample size of 76 (38 per group) is needed [30].

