## Abstract

Selective mutism (SM) is a relatively rare anxiety disorder, characterized by a child's consistent failure to speak in various specific social situations (e.g., at school), while being able to speak in other situations (e.g., at home). Prevalence rates vary from 0.2% to 1.9%. SM is usually identified between the ages of 3–5 years. It is often underdiagnosed and consequently children receive no or inadequate treatment, with negative consequences for school and social functioning. If left untreated, SM can result in complex, chronic anxiety and/or mood disorders in adolescence and impaired working careers in adulthood. Currently, no evidence-based treatment for SM is available in the Netherlands, therefore this study aims to [1] test the effectiveness of a treatment protocol for SM that is carried out at school, and to [2] identify baseline predictors for treatment success.

This article presents the design of a randomized controlled trial into the effectiveness of a behavioral therapeutic protocol for selective mutism in children (age 3–18). The expected study population is n = 76. Results of the treatment group (n = 38) will be compared with those of a waiting list control group (WCG) (n = 38). Pre and post treatment assessments will be conducted at comparable moments in both groups, with baseline assessment at intake, the second assessment at 12 weeks and post-assessment at the end of treatment. If proven effective, we aim to structurally implement this protocol as evidence-based treatment for SM.

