### Intervention

2.2

A standardized, behavioral therapeutic protocol was developed in the Netherlands to treat SM [16]. Children learn in different steps, by using gradual exposure to challenging situations, shaping and modelling. The advantage and innovative aspect of this protocol is that treatment is carried out solely at school. Since at school the problem is present most evidently, a therapist goes to school to practice individually with the child. This helps to generalize the learned exercises to the school situation. Every week the child learns step by step to make sounds and to speak, after which the speaking behavior is extended to various places in school with as the final goal: participating actively in the circle discussion in the classroom.

The protocol is mainly based on behavioral techniques, with as the primary aim stepwise practicing to speak. However, for children from 12 years and older, additional cognitive elements (e.g. helping thoughts) which are used in traditional cognitive behavioral therapy for anxiety [17], are available to be used optionally. The therapist involves the teacher as a co-therapist in the treatment process. After each weekly treatment session at school, the therapist instructs the teacher how profit can be maintained and which exercises to practice during the week. The teacher then continues the exercises throughout the week, finding short moments in time during the week to practice with the child. The therapist is in touch with the teacher face to face after each therapy session, by email or phone when necessary.

Previous clinical experience learns that the average treatment duration with this protocol is 22 weeks.

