### Assessments

2.3

Parents, children older than 8 years and teachers will complete questionnaires online. Parents will also be interviewed by the researcher.

The psychologist-researcher who performs the assessments will be blinded for participants’ allocated intervention. Children and parents, as well as the treatment-staff are explicitly asked not to talk about their randomization condition with the psychologist-researcher. Both groups are treated with the standard treatment protocol for selective mutism.

Assessments will be carried out at the following time points [1]: T1, baseline assessment during intake, before intervention starts [2]; T2, 12 weeks after baseline, either after first 12 weeks of treatment or 12 weeks of waiting list period [3]; T3, after last treatment session. If at any of the assessments or during the waiting list and/or treatment period there is sudden need for immediate intervention (e.g. in the event of a crisis), unblinding will take place to ensure that the participating patient receives the necessary care.

To acquire information from all informants (parents, guardians, teachers, children/adolescents), standardized questionnaires and interviews will be used with adequate psychometric properties, except for the Dutch translation of the SMQ, which will be validated in this study.

In Table 1, all assessments are listed.

**Table 1 tbl1:** Measures per assessment moment.

Instrument	Variable	Assessment moment		
		T1	T2	T3
Primary outcomes				
Selective Mutism Questionnaire (SMQ)	Selective mutism symptoms	P	P	P
Selective Mutism section of Anxiety Disorders Interview Schedule (ADIS-C)	Selective mutism symptoms	P	P	P
Secondary outcomes				
ADIS-C	Anxiety and mood symptoms	P	a	P
Child Behavior Checklist (CBCL)	Behavioral and emotional problems	P	P	P
Teacher Report Form (TRF)	Behavioral and emotional problems	T	T	T
Youth Self Report (YSR)	Behavioral and emotional problems	C	C	C
Self-Perception Profile Child/Adolescent (SPP–C/A)	Self-image	C		C
Child Health Questionnaire (CHQ)	Quality of life	P		P
Predictors				
Adult Self Report (ASR)	Behavioral and emotional problems	P		
EMBU-P	Parenting style	P		
Demographic variables	Demographics	P		
Health care consumption questionnaire	Health care consumption	P		

P: Parents.

T: Teacher.

C: Child.

SMQ: Selective mutism questionnaire.

ADIS-C: Anxiety Disorder Interview Schedule – Children's version.

CBCL: Child Behavior Checklist.

TRF: Teacher Report Form.

YSR: Youth Self Report.

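### The primary T1–T3 comparison between arms has no untreated control, because the waiting-list arm is also treated before T3; the controlled contrast is at T2

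*Protocol article*

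**What the plan says.** The sample size paragraph (end of section 2.5) names the primary outcome as "the pre versus post treatment change (T1-T3) on selective mutism symptoms". It derives 38 children per group from d = 0.58, two-tailed alpha 0.05 and power 0.8. Section 3.2 tests the primary outcome with a factorial repeated measures ANOVA on change between the "pretreatment and post treatment assessment of the treatment versus WCG group".

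Section 2.3 sets the schedule:

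- T2 is "12 weeks after baseline, either after first 12 weeks of treatment or 12 weeks of waiting list period".
- The last assessment is "T3, after last treatment session". No separate definition is given for the waiting list.
- "Both groups are treated with the standard treatment protocol for selective mutism".

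Section 2.2 reports from clinical experience that "the average treatment duration with this protocol is 22 weeks". The abstract says that "Pre and post treatment assessments will be conducted at comparable moments in both groups". Table 1 shows both primary measures, the SMQ and the ADIS selective mutism section, at T1, T2 and T3. The Background gives the aim as effectiveness relative to a waiting-list control group.

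**The concern.** A waiting-list trial can separate the treatment effect from maturation, school-year changes and regression to the mean only while one arm is still waiting. The plan puts its primary outcome and its sample size on a window that ends after treatment has finished. If the waiting-list arm has been treated by then, the comparison is treated now against treated later.

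Two errors could follow. A treatment that works equally well in both arms would give a null between-arm result. Alternatively, the improvement from T1 to T3 seen in both arms could be read as efficacy although nothing controls for change over time. The abstract and section 4.2 look ahead to structural implementation and wide roll-out, so either error would matter.

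**Working it through.** **1. The plan's own figure.** The inputs in the sample size paragraph are d = 0.58, two-tailed alpha 0.05, power 0.80 and 38 per group. A two-sample t-test with these inputs needs 47.6, so 48 per arm; 38 per arm gives power 0.70. The stated 38 is obtained with a one-sided test (37.5, rounded up to 38), or with baseline adjustment at a correlation of about 0.45: 47.64 × (1 − 0.45²) = 38.0. The article states neither. That mismatch is a separate matter. What counts here is that d = 0.58 is applied to a between-arm contrast ending at T3.

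**2. Where T3 falls in each arm.** The inputs are the 12-week waiting period (section 2.3) and the 22-week average course (section 2.2). It is inferred that waiting-list children begin treatment at T2.

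| Reading of T3 | Treatment arm | Waiting-list arm | Treatment received at T3 |
|---|---|---|---|
| After each child's own last session | week 22 | week 12 + 22 = 34 | 22 vs 22 weeks |
| Same calendar time, week 22 | week 22 | week 22 | 22 vs 22 − 12 = 10 weeks |

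Neither row contains an untreated arm. The first fits the wording of section 2.3 but not the abstract's claim of comparable moments. The second fits the abstract but not an assessment after the last session.

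**3. Size of the T1–T3 contrast.**

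- *Own-treatment reading.* With equal benefit in both arms the expected difference is about 0, so the rejection rate equals alpha, 5%. This restates the premise and is not independent evidence. For assumed residual differences of d = 0.1, 0.2 and 0.29, a two-sample t-test with 38 per arm has power 0.07, 0.14 and 0.24.
- *Calendar reading.* Assume that 0.58 is the effect of a full course and that gain is linear over 22 weeks. The difference is then 0.58 × (22 − 10)/22 = 0.32, and unadjusted power is 0.28.

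**4. Size of the T2 contrast.** This is 12 weeks of treatment against 12 weeks of waiting. With adjustment for T1, the effective standardised difference is d/√(1 − r²), where r is the T1–T2 correlation. The article gives no r, so a range is shown, for 38 per arm and two-sided alpha 0.05.

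| Effect at week 12 | r = 0.3 | r = 0.5 | r = 0.7 |
|---|---|---|---|
| Full d = 0.58: d/√(1 − r²) | 0.61 | 0.67 | 0.81 |
| Power | 74% | 82% | 94% |
| Linear gain, d = 0.58 × 12/22 = 0.32: d/√(1 − r²) | 0.33 | 0.37 | 0.44 |
| Power | 30% | 35% | 48% |
| Needed per arm for 80% power | 144 | 119 | 81 |

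Without adjustment, d = 0.32 would need about 158 per arm.

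**The case against.** Three points on the other side deserve weight.

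First, no sentence says when the waiting list starts treatment or how its T3 is timed. This stands: the sequence is pieced together from three statements in section 2.3. A reader might therefore take it as documented that both arms have completed the same course at T3. The text does not go that far, and under calendar alignment the contrast is diluted, not null. It does not rescue the endpoint, because neither timing leaves the waiting list untreated.

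Second, a reader might infer that the trial as a whole cannot show effectiveness. The documents do not support that. Both primary measures are collected at T2 in both arms, and section 3.2 does not list the time levels of the ANOVA. If T2 is a level, the group-by-time interaction contains the randomised treated-versus-waiting contrast. In a simulation with d = 0.58 at T2, no difference at T3 and equal correlations of 0.3, 0.5 and 0.7, that interaction had 57%, 73% and 92% power. But the sample size paragraph names T1–T3, and section 3.2 speaks of pretreatment and post-treatment assessments without naming T2. The defect is therefore in the named primary time point, not in the data collected.

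Third, moving to T2 is not simply a gain in power. The favourable figures assume that the full effect is reached about 12 weeks into a course averaging 22, and the article does not say to which time point d = 0.58 refers. This stands and shapes the fix.

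A reader might also suspect that treatment-arm T1–T3 will be set against waiting-list T1–T2, which would confound follow-up length with arm. Nothing in the article plans that.

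**Conclusion.** The point holds for the T1–T3 between-arm comparison and must be corrected: as written, it cannot deliver the stated comparison with a waiting list. The conclusion that the waiting list is not untreated at T3 rests on reading the statements in section 2.3 together. The week counts also use the 22-week average, so individual children will differ. The near-null result assumes equal benefit in both arms; the diluted result assumes linear gain with 0.58 as the full-course effect.

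The randomised treated-versus-untreated contrast is at T2 and remains available. How much power it has with 38 per arm is open, from about 30% to 94% over the assumptions shown.

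**What to change.** In the abstract, the sample size paragraph and section 3.2:

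- Name the between-arm difference at T2 (12 weeks), adjusted for T1, as the primary comparison for the primary measures already listed, the SMQ and the ADIS selective mutism section. Whether one of them should take precedence is a separate question that this change leaves alone.
- State that it estimates the effect of the first 12 weeks of treatment versus waiting.
- Report changes to T3 in either arm as uncontrolled pre-post description, without an effectiveness claim.
- Say when the waiting list starts treatment and how its T3 is timed, and reconcile this with the abstract's comparable moments.
- Restate the sample size for T2, with a justified 12-week effect and an assumed T1–T2 correlation.

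No new assessment is needed, because Table 1 already has both measures at T2. The cost is more than wording, however. The 12-week effect may be smaller than the end-of-treatment effect. Under linear gain, 81 to 144 per arm would be needed for 80% power, and even the aim of including 100 children (section 3.1), about 50 per arm, would fall short.

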Currently, it is still unclear which mechanisms affect treatment success in children with SM. For childhood anxiety disorders in general, it is known that parental factors (parenting style, parental psychopathology and previous health care consumption) can influence treatment success [7]. A study of Oerbeck, Stein [8] shows that children who are treated for SM at a younger age, show faster treatment progress than older children. These results were maintained on longer term [9]. In another study of Oerbeck, Overgaard [10], besides age, higher severity at baseline, familial anxiety and compliance of parents were predictors of treatment success. Also the predictive value of bilingualism, gender, comorbidity and minority status was investigated. These results were less compelling. As the authors also note, possibly due to a relative small sample size (N = 32) effect sizes were small. Especially at follow-up due to consequences of drop-out during the study. In our clinical institution we see a large, heterogeneous population of children with SM, with many bilingual children, as also described by Elizur and Perednik [4] and Toppelberg, Tabors [11]. Although several evidence-based treatments, based on (cognitive) behavioral therapy are available for anxiety disorders in children [12], studies investigating treatment effects in children with SM are still limited. A recent non-randomized trial showed that behavioral techniques with additional parent child interaction therapy improve SM symptoms [13]. Three previous randomized controlled trials (RCT) investigated showed that behavioral therapy was effective for selective mutism [8,14,15]. These studies provided therapy in different settings i.e. in the clinical setting [14,15] and at home before starting at school [8]. Unfortunately sample sizes in these studies are relatively small (N = 21, N = 24, N = 29). Currently, no evidence-based protocol specifically for the treatment of SM is available for the Dutch population. Since such a protocol is urgently needed in clinical practice, in our institution the protocol ‘Speaking in school, a matter of doing’ was developed [16]. A considerable strength compared to most previous studies is that this treatment is provided at school, where the problem is most present. The rationale is that treatment in school makes it easier to generalize speaking behavior to settings where the child still has difficulty speaking. In this RCT we aim to investigate the effectiveness of this behavioral therapeutic protocol, compared to a waiting list control group. A major methodological advantage is that we aim to execute a sufficiently powered RCT. Secondly, we aim to identify putative predictors for treatment success in children with SM.

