### Possible difference between participants and drop-outs

3.1

Clinical experience in this patient population shows us that drop-out during treatment is rare. To be able to compensate for possible drop-out during the study (if needed), we aim to include 100 participants as a safety measure. A drop-out analysis on the drop-out population will be conducted: it will be studied whether there are possible differences in variables (such as: gender, age, socio-economic status, bilingualism, severity of selective mutism at baseline assessment and parental psychopathology) between the population that participates until the end of their treatment and the population that drops out. In this way it can be checked whether there is a selective dropout. A selective dropout can lead to selection bias, which could be statistically adjusted for.

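### The stated inputs (d = 0.58, two-tailed alpha 0.05, 80% power) need 96 children, not 76; 38 per group gives about 70% power

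*Protocol article*

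**What the plan says.** The Sample size calculation paragraph (an unnumbered heading after section 2.5) takes d = 0.58 from an earlier randomised trial of behavioural treatment. It applies this effect to the primary outcome, described as "the pre versus post treatment change (T1-T3) on selective mutism symptoms". The remaining inputs and the conclusion stand in one run: "an alpha of 0.05 (two-tailed) and a power of 0.8, a sample size of 76 (38 per group) is needed". No pre-post correlation, covariate adjustment or other reduction in variance is mentioned.

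The same size appears elsewhere. The Abstract says "The expected study population is n = 76", and section 2.1 assigns 38 children to each arm. Section 3.1 calls drop-out rare and adds "we aim to include 100 participants as a safety measure", to be used for drop-out if that proves necessary. Section 3.2 names a factorial repeated measures ANOVA for the primary outcome. The Background points to the small samples of earlier trials (21, 24 and 29) and counts it as a major methodological advantage that "we aim to execute a sufficiently powered RCT".

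**The concern.** Every input for checking the figure stands in the sentence that gives it, and 38 per group looks too small for d = 0.58 in a two-tailed test. If it is too small, a team that stops at 76 will believe it has a 20% risk of missing the assumed effect when the risk is larger. Readers would also be given a power statement that the design does not meet, in an article that sets this trial apart from its predecessors by its power. The trial is meant to decide whether the treatment is adopted as evidence-based care, so a null result would be read in the light of that statement.

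**Working it through.** **Inputs.** d = 0.58, alpha 0.05 two-tailed and power 0.80 (Sample size calculation paragraph); 1:1 allocation (section 2.1). Because d is applied directly to the T1-T3 change, the group comparison of change is a two-sample t test with standard deviation 1.

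**Does the plan's figure reproduce?** The normal approximation is n per group = 2(z₁ + z₂)²/d².

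- Two-tailed: 2 × (1.960 + 0.8416)²/0.58² = 2 × 7.849/0.3364 = 46.7, so 47 per group.
- One-tailed: 2 × (1.645 + 0.8416)²/0.58² = 2 × 6.183/0.3364 = 36.8, so 37 per group.

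The exact calculation uses the noncentral t distribution with 2n − 2 degrees of freedom and noncentrality d√(n/2):

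- Two-tailed: 47.64, so 48 per group and 96 in total.
- One-tailed: 37.45, so 38 per group and 76 in total.

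The two-tailed inputs do not give 38. The one-tailed exact calculation does.

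**Power at various sizes, d = 0.58 (noncentral t).**

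| n per group | Total | Two-tailed | One-tailed |
|---|---|---|---|
| 37 | 74 | – | 0.796 |
| 38 | 76 | 0.704 | 0.805 |
| 47 | 94 | 0.7945 | – |
| 48 | 96 | 0.803 | – |
| 50 | 100 | 0.819 | 0.892 |

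Hand check at 38 per group: the noncentrality is 0.58 × √19 = 2.528, and 2.528 − 1.960 = 0.568. The normal approximation then gives 0.715, against 0.704 from the t distribution.

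**Detectable effect.** At 38 per group, two-tailed, 80% power requires d = 0.651.

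**Shortfall.** 96 − 76 = 20 children, and 96/76 = 1.26, so 26% more than stated. The type II error is about 0.30 instead of 0.20.

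**The aim of 100.** With all 100 evaluable, power is 0.819. Power stays at 80% or more down to 48 per group, so the margin is 100 − 96 = 4 children, two per arm. If the reserve were used up (100 − 76 = 24 losses), power would be back at 0.704.

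**The case against.** The strongest reply is that the planned analysis is a repeated measures ANOVA, and that repeated measurement can reduce the number needed. The paragraph names no test and refers to a source that is not at hand. If d = 0.58 is standardised on the raw-score standard deviation, the result depends on the T1-T3 correlation r, which the article does not give. Taking r as an assumption:

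- Change score or group-by-time test, effective d = 0.58/√(2(1 − r)): power at 38 per group is 42% at r = 0, 70% at r = 0.5 and 79.7% at r = 0.6.
- ANCOVA on baseline, effective d = 0.58/√(1 − r²): power is 79.8% at r = 0.45 and 82.2% at r = 0.5. Section 3.2 does not plan this analysis.
- Group-by-time effect entered as f = d/2 = 0.29 with two time points: 50 children in total at r = 0 and 26 at r = 0.5. Neither is 76, and this f implies a between-group difference in change of 4 × 0.29 = 1.16 raw standard deviations, twice the stated effect.
- Between-group test averaged over three time points: 78 in total at r = 0.7, but it does not test change.

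What stands is that 76 could be defended under an assumption the article does not make. On its plain reading d refers to the change itself, and the power is then 70%.

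The second reply is that 100 children are intended and drop-out is expected to be rare, so the realised power may well be near 80%. That is fair. A reader might infer that the trial will run at 70% power; the article does not support that, because 70% applies if it ends with 76 evaluable children. But the 100 is conditional and reserved for drop-out, while the Abstract and section 2.1 keep 76 and 38 per group. It does not make the sentence correct.

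**Conclusion.** The sample size statement is wrong as written. Its own inputs require 48 per group (96 in total) for a two-group comparison, and 38 per group gives about 70% power, some 10 points below the stated 80%. This rests on 1:1 allocation and on d = 0.58 applying directly to the T1-T3 change. The choice between exact and approximate formulas moves the requirement by only one child per group.

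Two stronger readings are not supported. A reader might infer that a one-tailed test was used by mistake. The match with 38 is exact, but the article says two-tailed and gives no account of the cause, so this is only a possible explanation. A reader might also infer that power is presented as the trial's main advantage; the Background calls it a major one.

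**What to change.** Restate the Sample size calculation paragraph: 76 children (38 per group) give about 70% power two-tailed for d = 0.58, and 80% requires 96 evaluable children. Qualify the claim of sufficient power in the Background accordingly.

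Optionally, make the already intended 100 the fixed randomisation target, align the Abstract and section 2.1 with it, and state that 80% then holds only with at most 4 losses, balanced between the arms. This uses up the drop-out reserve, so a larger expected loss would need a larger target.

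If the authors prefer to keep 76 at 80%, they should state and justify a pre-post correlation for the T1-T3 endpoint and the analysis actually planned. That means about 0.6 for a change-score or group-by-time test with d on the raw-score standard deviation. A correlation of about 0.45 to 0.5 would suffice only if the primary analysis were changed to ANCOVA.

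The cost is one corrected paragraph, a matching edit in the Background and a less favourable stated power. No enrolment beyond the intended 100 is needed as long as losses stay within 4.
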